## Abstract

**Introduction:**

There are approximately 700 000 autistic people in the UK, and autism is increasingly being diagnosed in adulthood. Diagnosis on its own does not provide adequate information to plan post-diagnostic support for autistic people, and clinicians often plan support without the use of validated standardised tools which may exacerbate inequities in care. This study will evaluate a novel strengths and needs assessment, based on the WHO’s International Classification of Functioning, Disability and Health CoreSet for Autism, for use in adult diagnostic services immediately on receipt of an autism diagnosis. Potential issues, including the length of the assessment, timing of delivery and selection bias, will be explored as part of the trial process evaluation.

**Methods and analysis:**

A two-arm, multisite, randomised pilot trial design will be used to evaluate the ICF CoreSets for Autism Strengths and Needs Assessment in three diagnostic services in England. A total of 72 newly diagnosed autistic adults will be recruited across the three sites over a 6-month period and randomised into an assessment group (strengths and needs assessment plus standard care) and a treatment as usual group (standard care only). The assessment group will receive a summary report of their strengths and needs on completion of the assessment. Both groups will complete measures of mental health and quality of life at baseline and 3 months follow-up (Patient Health Questionnaire-9, Generalised Anxiety Disorder questionnaire-7, Recovering Quality of Life questionnaire-10, EuroQoL-5D). Acceptability and feasibility will be measured for the strengths and needs assessment and for trial procedures using standardised measures, progression criteria and qualitative data from clinician focus groups and interviews with a subsample of autistic participants. The study design and procedures are being co-produced with an autistic advisor/patient and public involvement lead and with a steering group of autistic adults.

**Ethics and dissemination:**

This study was reviewed by the East Midlands—Nottingham 2 Research Ethics Committee and was given Health Research Authority approval on 18 March 2025 (REC reference:25/EM/0041). The results will be disseminated via reports to the funder (NIHR), a peer-reviewed journal paper and academic conferences. We will email a summary report of findings to study participants and will invite participants to an information dissemination event at the end of the study. Links to reports and a lay summary will be provided on the research group’s website: https://sharl.sites.sheffield.ac.uk/home

**Trial registration number:**

ISRCTN10283350.

STRENGTHS AND LIMITATIONS OF THIS STUDYRandomisation methods will allow groups to be balanced for age, gender and ethnicity and will avoid the risk of selection and allocation bias.The study will be co-produced with autistic adults to ensure that study procedures are acceptable and coherent to the autistic community.Blinding of clinicians to study participation and allocation may prove difficult due to ongoing contact with participants.Half of the sample will not complete the assessment, which could lead to higher attrition in the treatment as usual arm.The length of the assessment and timing of delivery could be burdensome for some participants.

## Introduction

 There are estimated to be around 700 000 autistic people in the UK,^1^ although research on underdiagnosis suggests that this number could be much higher.^2^ Recorded autism diagnoses rose from 1 to 20 per 100 000 adults in the UK over a recent 20-year period (1998–2018) and autism is increasingly being diagnosed in adulthood.^3^

Most adult autism diagnoses in the UK are made by secondary care diagnostic services following referral from a general practitioner (GP) and an assessment in the diagnostic service. Autistic adults are then given their diagnosis and, sometimes, offered post-diagnostic support. A diagnosis of autism does not, on its own, provide sufficient information to determine what the most appropriate post-diagnostic support would be for an individual.^4^ At present, there is no standardised way of assessing autistic people’s strengths and needs,^5 6^ which means that clinicians cannot direct people to support and resources based on their individual needs using a standardised tool.

Diagnostic services have different post-diagnostic care pathways for their service users which may include signposting to resources, psychoeducational input and support sessions. However, post-diagnostic support is geographically inequitable^5^ and, in general, considered inadequate both by autistic people^7 8^ and clinicians.^9^ The lack of a standardised pathway for providing post-diagnostic support means that clinicians are also having to spend large amounts of time and service resources in creating bespoke service-specific offerings.^5^ The Department of Health and Social Care (2021–2026) strategy^10^ specifies improving the quality of post-diagnostic support for children and adults as a priority.

Working towards preventing the perpetuation of health inequalities and ensuring that autistic people get better support are also part of the National Health Service (NHS) long-term plan.^11^ Indeed, autistic adults often face worse outcomes than neurotypical adults in a range of areas, including employment,^12^ mental health,^13^ inpatient admissions^14^ and premature mortality.^15^ With early support, it may be possible to mitigate these poorer outcomes and promote effective self-management.^16^

Research suggests that autistic people prioritise an individualised support plan as part of their post-diagnostic support package,^6 17^ which could facilitate a more balanced and thorough understanding of what their diagnosis means to them. It could also be used to communicate their support needs to others (eg, employers, healthcare providers, educators), as well as highlighting what their strengths are.

This study will trial a novel strengths and needs assessment for autistic people in diagnostic settings in the UK. The assessment has been developed from the International Classification of Functioning, Disability and Health (ICF) which was developed by the WHO^18^ to measure health and disability in individuals and populations, covering four main areas (body functions, body structures, activities and participation, environmental factors). The ICF is ratified by 191 countries as the global standard for assessing functioning. It therefore provides a standardised and shared language which can be used in a variety of settings (eg, education, health, social services).^19^ It also aligns with the priorities of neurodiverse people to facilitate a move from a deficits-based focus on symptoms and impairment to a more holistic approach which also captures capabilities and strengths, as well as considering the important role of environmental factors.^20^

The comprehensive ICF framework is extremely long (almost 1700 codes) and is therefore very difficult to use in practice.^21^ For this reason, CoreSets have been developed which include only the items most relevant to particular diagnoses and settings. For example, CoreSets have been developed for a number of specific diagnostic groups (eg, strokes,^22^ hearing loss^23^) and are being used as a framework in the NHS (eg, stroke rehabilitation)^24^ to facilitate goal setting and action planning.

Coreset development follows a rigorous protocol outlined by the WHO and aims to represent the perspectives of stakeholders.^25^ Following a process of consensus building with experts and autistic stakeholders, the CoreSets for autism and Attention Deficit Hyperactivity Disorder (ADHD) were published in 2019 and are available to guide clinical practice and research.^26^ In response to criticisms that there was a lack of guidance for professionals in how to apply the CoreSets^27^ and to move away from lists of codes, the ICF CoreSets platform was developed (icfcoresets.se). This is a user-friendly platform with a range of versions of the ICF CoreSet, for autism and ADHD (or combined), for different age ranges, and for self or proxy report. The CoreSet has reduced the number of functional codes from the full ICF framework to 110 (7% of all ICF codes).^28^ The most recent version of the online assessment has a total of 265 items derived from these ICF codes. In mitigation for the length of the assessment, the platform allows users to complete it in as many sittings as they wish, as responses are saved continually.

The online assessment has been evaluated for acceptability and feasibility of delivery in the UK and in Sweden and has been generally positively received by autistic people both for usability and for potential benefit. In the UK, it was piloted with groups of autistic adults for supported face-to-face completion (with a researcher, n=20) and for online self-completion (n=464). Acceptability and usability of the assessment were measured using the System Usability Scale (SUS)^29^ and the Theoretical Framework of Acceptability (TFA)^30^ and were found to be acceptable and usable for both supported and self-completion.^31^ The completion rate for autistic people was 91% and median completion time was 34 min, although times varied a great deal depending on the extent to which participants added additional text responses.

In Sweden, the assessment has been found to be acceptable and easy to navigate by a sample of 678 respondents (311 neurodiverse, 367 neurotypical) via self and proxy report. The assessment was positively appraised for the inclusion of environmental factors and the ability to highlight strengths.^28^ During these pilots, respondents gave qualitative feedback about issues with the assessment which were addressed in a revision to the online platform in 2024.^32^ The psychometric properties of the assessment have also been evaluated and show it is a valid and reliable measurement tool which demonstrates consistency in inter-rater reliability, has good internal consistency for subdomains, can effectively distinguish between neurodivergent groups and the general population, and aligns with diagnostic criteria.^33^

This work shows the potential of the ICF CoreSets online platform in providing a standardised approach to measuring functioning in autistic people. It is important to now move this work on by exploring the utility of the assessment in different settings. This study will therefore evaluate the most recent version of the Strengths and Needs Assessment (ICF CoreSet for Autism)^32^ delivered in post-diagnostic settings in the UK. On completion of the assessment, a summary report is produced which organises the answers given by participants into areas of strength and areas of need across the categories of body functions, activities and participation, and environmental factors. This could be used to manage support needs in a range of contexts (eg, employment, education, health) and aligns with the priority of autistic people for a personalised support plan following their diagnosis.^6 17^

The primary aim of this study is to assess the acceptability and usability of the ICF CoreSets for Autism Strengths and Needs Assessment for autistic adults and clinicians, specifically when administered for self-report, at the point of receipt of an adult autism diagnosis. Previous pilots of the assessment in the UK have not provided the summary report, so this will be the first indication of the acceptability and potential benefit of this aspect of the assessment.^31^

The study will also evaluate the acceptability and feasibility of the trial design in preparation for a future definitive randomised control trial (RCT). The UK’s Medical Research Council’s framework for evaluating complex interventions^34^ highlights the importance of piloting prior to larger efficacy trials being carried out. This identifies potential problems which could lead to underpowering in larger trials and provides estimates for trial sample sizes. Acceptability will be evaluated in interviews with participants and focus groups with clinicians. The feasibility of the proposed recruitment, randomisation and data collection methods will be evaluated against a list of progression criteria before planning for a future trial.

Specifically, the research questions are

RQ1a: Are the proposed recruitment, randomisation and data collection methods acceptable and feasible for use within NHS adult autism diagnostic services?

RQ1b: Is the ICF CoreSets for Autism Strengths and Needs Assessment acceptable for use by autistic adults on receipt of an autism diagnosis?

RQ1c: What are the potential benefits or harms of completion of the ICF CoreSets for Autism Strengths and Needs Assessment?

The secondary aim is to gain a thorough understanding of the characteristics and mental health status of the populations receiving autism diagnoses in these clinical settings. We will use mental health and quality of life (QoL) outcome measures to answer the secondary research question:

RQ2: What are the demographics and current mental health status of adults being diagnosed in NHS services?

Mental health measures will also be used to monitor for adverse events arising from study participation. They will also provide preliminary data on whether the strengths and needs assessment improves well-being outcomes and how feasible it is to use these measures to measure efficacy in a larger trial.

The study will be reported according to Consolidated Standards of Reporting Trials guidelines for reporting randomised pilot and feasibility trials.^35^ If effective, the ICF CoreSets for Autism Strengths and Needs Assessment have the potential to be implemented in NHS diagnostic services as a standardised approach to providing post-diagnostic support for autistic adults.

## Methods and analysis

### Design

A two-arm, multisite, RCT is being piloted in three NHS autism diagnostic services in the UK (Leeds Autism Diagnostic Service (LADS); Cambridgeshire Lifespan Autism Spectrum Service; Sheffield Adult Autism and Neurodevelopmental Service (SAANS)). The research team is based in the Sheffield Autism Research Lab at the University of Sheffield. The sponsor of the study is Sheffield Health Partnership University NHS Foundation Trust. The trial has been registered in the ISRCTN platform (ISRCTN10283350) and has been approved by the NHS’s Health Research Authority in the UK (IRAS:350522).

### Patient and public involvement

Autistic adults have been and will continue to be involved at all stages of this study, including project design and planning, methods of data collection and sharing of findings with the autistic community. The patient and public involvement (PPI) lead for the project is an autistic adult with expertise in eliciting the views of autistic participants. An autistic steering group will meet at various stages throughout the project to aid in the design of written materials, interviewing methods, study procedures and dissemination of results. This group advised on the burden of completing the assessment and on considerations around presenting it during the immediate post-diagnostic period.

### Study settings

The three participating NHS settings are secondary care settings which receive referrals for autism assessments from GPs, other clinicians (eg, community mental health teams), family and self-referrals. Referrals are mainly for adults but also include some 16- and 17-year-olds. LADS also has a pathway for referrals from individuals with intellectual disabilities. These sites carry out autism assessments, deliver the results to service users and provide initial post-diagnostic support.

### Participants

The trial will recruit 72 autistic adults who have received a diagnosis of autism from one of the three participating clinical services (24 in each service). Participants will be adults (18+years) and will not have a diagnosis of a co-occurring learning disability. Clinicians will not invite individuals with a diagnosed intellectual disability to take part in the study. Participants will be recruited over a 6-month period from 1 April 2025 until 1 October 2025 or until the service target sample (24) has been recruited. The sample size is in line with guidance recommending a sample size of 70 for a two-arm randomised pilot study.^30^

### Study procedures

Service users who receive a diagnosis of autism and meet the other eligibility criteria (18+ years old, no diagnosis of intellectual disability) will be given information about the study (written information leaflet, verbal information) by their diagnosing clinician which includes links to access further information about the study and contact details for the research team at the University of Sheffield. This will be given alongside other standard care information (eg, signposting to resources, information about their service’s post-diagnostic provision) at the appointment where they receive their diagnosis. The full information sheets for the study have been provided in standard and Easy Read/Plain English versions. Participants will have 4 weeks from the date of their diagnosis to decide whether they would like to participate in the study. They will be able to access a form to consent to participate and to provide their contact details via the links provided in the information leaflet.

Participants will be emailed a link to complete a short demographic questionnaire (age, gender, ethnicity, diagnosing service, date of diagnosis). Following this, they will be randomised into either the assessment group (n*=*36) or the treatment as usual group (n*=*36) by the research team at the University of Sheffield. This will be done using a minimisation approach which allows demographic factors to be balanced across groups in ongoing recruitment. This will be done using software developed by researchers at the University of York^36^ and will balance three factors (gender, age, ethnicity) with two levels for each factor (male/female, under/over 40, white/non-white) in each study arm. All participants will continue with the standard care offered by their clinical site during the study. This may include signposting to resources, follow-on appointments and psychoeducational input. It is not possible to blind participants to group allocation. However, clinicians will not be informed about individual participation or group allocation.

Both groups will complete online QoL and mental health questionnaires at baseline (T1) and at 3 months follow-up (T2). Only the assessment group will be asked to complete the strengths and needs assessment. A link to complete the strengths and needs assessment will be emailed immediately after baseline measures are completed. Participants will be told that they can email the researcher with any questions about the assessment or to provide support during the completion process. They will also be told that they can do the assessment in as many sittings as they choose to (responses are saved on the platform continually) and that they can complete the assessment over a 2-week period.

Participants will receive voucher payments of £20 for completing their T1 measures and £10 for completing T2 measures. Participants who do not complete measures will receive a reminder email with contacts for the research team at the University of Sheffield and links to support services.

A subsample of 12 participants (four from each service: two from the Assessment group and two from the treatment as usual group) will also be invited to take part in an interview after T2. They will be provided with additional information for these interviews and will be asked to consent to take part. The interviews will be held mainly online, although some will be hosted in the diagnostic services, if participants prefer, and services have capacity to offer this. The interviews will follow a semi-structured schedule which will cover the acceptability and feasibility of the study procedures and the strengths and needs assessment, any barriers or facilitators to trial participation, any adverse effects of participation and their personal experiences of post-diagnostic support. Interviews will last for around 30 min and will be recorded and transcribed verbatim. Participants will receive voucher payments of £20 for taking part in an interview. Participating clinicians and administrators (involved with the set up or running of the study at each site) will be invited to take part in a focus group at each diagnostic service following the 6-month data collection period. Figure 1 shows the movement of participants through the study.

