### Data analysis

Descriptive data for all demographic variables will be presented by trial arm to provide an overview of the cohort of participants recruited to the study, to evaluate the group allocation methods and to demonstrate the representativeness of the sample. Means and SD will be reported for the QoL and mental health measures. These will be compared with clinical cut-offs to indicate levels of well-being in the sample.

Eligibility rate, recruitment rate, completion rates and times for the strengths and needs assessment and the outcome measures will be reported descriptively. Sample medians will be used as an estimate of average completion times. CIs will indicate completion time variance.

Participants will be given 2 weeks to complete the strengths and needs assessment and the QoL/mental health measure questionnaire. After 1 week, they will be sent a reminder and offered support if they need it. After 2 weeks, they will be considered ‘lost to contact’ and will be sent a debrief form with links to support organisations. The number of participants ‘lost to contact’ or withdrawn will be recorded as part of the trial evaluation. If participants start but do not complete the strengths and needs assessment, we will record the time they spend on the assessment and the proportion completed. Any data previously given by participants who are ‘lost to contact’ or withdraw will still be analysed unless participants ask us to withdraw their data.

Preliminary effectiveness of the strengths and needs assessment will be assessed using mixed model analyses of covariance. These analyses will determine whether QoL (assessed using EQ-5D-5L and ReQoL-10) and mental health (assessed using PHQ-9 and GAD-7) changes between baseline and 3 months post-intervention are affected by allocation to the assessment/TAU group. The analyses will statistically control for demographic variables and clinical site. Effect size will be reported using partial eta-squared which will inform the sample size calculation for the definitive trial (RCT).

Qualitative data from the interviews and focus groups will be analysed using NVivo.^45^ Questions pertaining to acceptability and feasibility of the trial procedure will be analysed using thematic content analysis.^46^ Experience of post-diagnostic service provision more generally will be analysed using a reflexive thematic analysis approach.^47^

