It is also possible that there could be higher attrition in the treatment as usual group as they will not be offered the chance to complete the ICF CoreSets for Autism Strengths and Needs Assessment. Higher levels of attrition in control arms of RCTs have been reported.^52^ To mitigate this risk, all the participant information sheets emphasise the importance of having a control group. Both the assessment and treatment as usual groups will also receive the same payment for taking part in the study. Whether being placed in the treatment as usual group is a disincentive for participation will be explored further in the interviews with a subset of participants as part of the trial process evaluation.

As participants self-select into the study, this may lead to some selection bias due to particular groups being less likely to enrol. To explore this, we will record demographic information about age, gender and ethnicity. As well as using this data to balance the assessment and treatment as usual groups, we will also use it to demonstrate the representativeness of our sample. As this is a feasibility trial, this will be helpful in planning a future trial and may suggest groups who might require more support to take part. As clinical sites record the numbers of leaflets they distribute, it will be possible to report recruitment rates (eligibility/number recruited). To address digital exclusion, we will offer participants who are not able to complete the study on a computer or phone the option of completing measures via post or supported by a researcher in their clinical setting.

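### The T1 baseline is collected after randomisation from participants who cannot be blinded, so loss before T1 is post-randomisation loss and T1 answers are open to influence by allocation

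*Protocol article*

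**What the plan says.** Study procedures gives the order. After consent: "Participants will be emailed a link to complete a short demographic questionnaire (age, gender, ethnicity, diagnosing service, date of diagnosis"). Next: "Following this, they will be randomised into either the assessment group", or the treatment as usual group, using minimisation on gender, age and ethnicity. On masking: "It is not possible to blind participants to group allocation".

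Only then do the mental health and quality of life measures appear: "Both groups will complete online QoL and mental health questionnaires at baseline (T1) and at 3 months follow-up (T2"). For the assessment arm: "A link to complete the strengths and needs assessment will be emailed immediately after baseline measures are completed".

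The Data analysis section sets the time limit: "Participants will be given 2 weeks to complete the strengths and needs assessment and the QoL/mental health measure questionnaire". It continues: "After 2 weeks, they will be considered ‘lost to contact’ and will be sent a debrief form with links to support organisations". The same section uses T1 as the baseline for mixed model analyses of covariance of change to 3 months by arm. It reports partial eta-squared to inform the definitive trial's sample size.

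Under Primary outcome measures, the attrition rate in each arm is among the data on trial feasibility. The Discussion raises possible higher attrition in the treatment as usual arm and plans to explore this in interviews: "Whether being placed in the treatment as usual group is a disincentive for participation".

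**The concern.** A baseline is protected by randomisation only if it is fixed before allocation. Here T1 precedes the assessment but follows randomisation, and all four instruments are self-report. Three things follow.

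- **Missing baselines.** A participant who stops between allocation and T1 is randomised but has given only demographic and diagnosis details. The balance achieved by minimisation need not hold among those who complete T1.
- **Attrition by arm.** Loss directly after allocation and loss during the 3-month follow-up have different causes and different remedies in a definitive trial. Both fall within arm-specific attrition unless they are counted separately.
- **T1 scores.** If participants know their arm when they answer, T1 may partly reflect that knowledge. This would reach the preliminary effect estimate, its partial eta-squared, and the RQ2 description of mental health status in so far as it uses T1.

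The first two follow from the stated order alone. The third also depends on when allocation is disclosed.

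**Working it through.** **1. Order of events (Study procedures).** Consent; demographic questionnaire; minimisation to 36 and 36; T1 questionnaires; assessment link to one arm; T2 at 3 months. No section places T1 before randomisation, and none says that allocation is withheld until T1 is submitted. The minimisation factors all come from the demographic questionnaire. That explains why allocation can run before T1, but it does not require that order.

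**2. Loss before T1 (illustration).** The article gives no T1 completion rate. Assume 5% loss before T1 in the assessment arm and 20% under treatment as usual:
- assessment: 36 × 0.95 = 34.2
- treatment as usual: 36 × 0.80 = 28.8
- total: 63.0 of 72, so 9 randomised participants would have no baseline.

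With no loss in one arm and 10% in the other the total is 36 + 32.4 = 68.4. With 10% and 30% it is 32.4 + 25.2 = 57.6.

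**3. Bias if allocation is known at T1 (illustration).** The article gives no SD, T1-T2 correlation or expected effect, so every input here is assumed: no true effect, equal SDs at T1 and T2, correlation ρ, and a shift s (in SD units) at T1 in the treatment as usual arm only. Let a fraction k of the shift persist to T2. For assessment minus treatment as usual:
- change score: bias = (1 − k)s
- ANCOVA on T1: bias = (ρ − k)s

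Both are shown because the article describes an analysis of change by mixed model analysis of covariance without settling how T1 enters.

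| s | change, k = 0 | ANCOVA, k = 0, ρ = 0.6 to 0.7 | change, k = 1 | ANCOVA, k = 1, ρ = 0.7 to 0.6 |
|---|---|---|---|---|
| 0.1 | 0.10 | 0.06 to 0.07 | 0 | −0.03 to −0.04 |
| 0.2 | 0.20 | 0.12 to 0.14 | 0 | −0.06 to −0.08 |
| 0.3 | 0.30 | 0.18 to 0.21 | 0 | −0.09 to −0.12 |

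The sign under ANCOVA therefore depends on how much of the reaction persists, and the bias vanishes when k = ρ.

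**4. Size against the pilot's precision.** With 36 per arm, SE(ANCOVA) = √(2(1 − ρ²)/36):
- ρ = 0.6: √(2 × 0.64/36) = 0.189
- ρ = 0.7: √(2 × 0.51/36) = 0.168

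The 95% half-widths are 1.96 × 0.189 = 0.37 and 1.96 × 0.168 = 0.33 SD. For k = 0 and ρ = 0.6 to 0.7, a normal approximation at two-sided 5% gives a false-positive rate of 6.2% to 7.0% at s = 0.1 and 15.9% to 23.9% at s = 0.3. The corresponding spurious partial eta-squared runs from about 0.0015 to 0.022.

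**5. With T1 before minimisation.** T1 cannot depend on allocation, so s = 0 at T1 and every randomised participant has a baseline. A reaction at T2 would remain possible, as in any unblinded trial with self-reported outcomes.

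**The case against.** The strongest reply is that distortion of T1 answers needs participants to know their arm at T1, and the article never says when they are told. That they cannot be blinded means they will learn their arm, not that they know it by T1. The only arm-specific contact described is the assessment link, sent once T1 is done, which is compatible with later disclosure. Figure 1 is not available here and may settle it. This stands: the reporting effect is conditional. It does not remove the loss problem, because someone who drops out before T1 has still been randomised.

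A reader might infer that the authors predict disappointment in the treatment as usual arm. They do not. They mention only possible higher attrition and say nothing of altered answers.

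A reader might also take 0.1-0.3 SD as an established bias. It is an assumption, and the full value applies to change scores only if T2 is unaffected. The assumed ANCOVA biases are also smaller than the pilot's 95% half-width. That stands for interpreting this pilot, although bias, unlike random error, would not shrink if the same order were used in a larger trial.

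The protocol does offer some protection: equal payment across arms, £20 attached to T1, information-sheet wording on the control group, and reporting of completion rates and attrition by arm. T1 and T2 losses can therefore be separated if the report chooses to. None of these changes the order.

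Finally, the acceptability and usability ratings do not use T1 scores, and the effectiveness analysis is preliminary and secondary. This limits the severity.

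**Conclusion.** The point holds, at moderate severity. As written, the baseline is a post-randomisation self-report from participants who cannot be blinded. Losses before T1 leave randomised participants without baseline or outcome scores and enter a primary feasibility outcome. This rests on the stated order alone.

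Influence of allocation on T1 answers, and non-completion prompted by knowing the arm, are possible but not shown, since the time of disclosure is not given. If they occur, neither the size nor the direction can be fixed from the article. Under the assumed shifts, ANCOVA bias ranges from +0.06 to +0.21 SD when T2 is unaffected, and from −0.03 to −0.12 SD when the shift persists fully.

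The stronger reading, that the pilot's results are already known to be biased or that its main conclusions fail, is not supported. The matter deserves correction because the pilot exists to test the procedures and supply the planning figures for a definitive trial.

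**What to change.** Send the T1 questionnaires together with the demographic questionnaire. Run the minimisation only once T1 is submitted, then disclose allocation and send the assessment link to the assessment arm. Report people who consent but do not complete T1 as a pre-randomisation loss.

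The cost is a reordering of emails and a small amendment. The minimisation factors are unaffected, and the assessment link already waits for T1, so that step is not delayed. The downside is that a few consenters who never complete T1 will not be randomised.

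If recruitment is too advanced for this, withhold allocation until T1 is submitted, state when disclosure took place, and report loss before T1 by arm separately from loss between T1 and T2. The definitive trial should use the corrected order.
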